## Abstract

**Abstract:**

**Introduction:**

Non-communicable diseases, particularly cardiovascular diseases (CVDs), have become major contributors to morbidity and mortality in sub-Saharan Africa (SSA) and are projected to surpass infectious diseases as the leading cause of death among adults by 2030. Although CVDs have traditionally been associated with older age and obesity, adverse cardiovascular phenotypes are increasingly being observed in younger and leaner individuals in SSA. This pattern suggests that pathways to CVD risk in SSA may differ from those described in high-income countries. Early-life infectious exposures, undernutrition and socio-demographic conditions common in many SSA settings have been proposed as potential risk factors. Still, empirical evidence linking these exposures to cardiovascular risk in early adulthood remains limited due to a scarcity of long-running birth cohorts in the region.

**Methods and analysis:**

This protocol describes a new round of data collection nested within the Entebbe Mother and Baby Study (EMaBS), a population-based Ugandan birth cohort established originally as a clinical trial (ISRCTN32849447) between 2003 and 2006 with prospective follow-up from pregnancy through adolescence. All participants currently under follow-up will be invited to participate at approximately 21 years of age. Primary outcomes are physiological determinants of CVD measured in early adulthood, including blood pressure, blood lipid levels, body mass index, body composition and markers of glucose metabolism. Secondary outcomes include behavioural CVD risk factors (diet, physical inactivity, alcohol use and tobacco use) and qualitative measures of CVD knowledge and risk perception. Key exposures of interest include prospectively collected early-life and childhood infectious exposures (malaria and helminth infections), markers of growth and undernutrition, micronutrient status, inflammatory markers, socio-demographic factors and selected genetic variants. Quantitative analyses will use multivariable regression and causal modelling approaches and will be complemented by qualitative interviews and focus group discussions.

**Ethics and dissemination:**

The study protocol has been reviewed and approved by the Uganda Virus Research Institute Research and Ethics Committee (UVRI REC Ref: GC/127/35), the Uganda National Council for Science and Technology (UNCST Ref: MV625), and the London School of Hygiene & Tropical Medicine Research Ethics Committee (LSHTM Ethics Ref: 8811). Written informed consent will be obtained from all participants before study activities. Study findings will be shared and discussed with participants and community stakeholders through established engagement platforms. Results will be disseminated to the scientific community through peer-reviewed publications and conference presentations, and data will be made available to other researchers via established data-sharing platforms. We will engage policymakers at the district, national and international levels to facilitate the translation of findings into policy-relevant outputs.

STRENGTHS AND LIMITATIONS OF THIS STUDYThis study builds on one of the longest-running and largest birth cohorts in low-income sub-Saharan Africa, with prospective data collected from the prenatal period through early adulthood.The cohort includes detailed longitudinal data on nutritional, infectious, growth and socio-demographic exposures.In addition to stored biological samples and genetic and epigenetic data, the longitudinal data of the cohort will be expanded with this new round of data collection.Due to strong participant and community engagement, the cohort has maintained support for long-term participant retention.One potential challenge is achieving the target sample size, given that recent nested studies within the Entebbe Mother and Baby Study have involved smaller participant groups, which may potentially lead to selection bias.

## Introduction

 Non-communicable diseases (NCDs), including cardiovascular diseases (CVDs), diabetes and cancer, are the leading cause of death globally. In sub-Saharan Africa (SSA), they are projected to overtake infectious diseases as the primary cause of adult mortality by 2030,^1^ with CVDs emerging as the leading contributor. This rising burden of CVDs has been largely attributed to the epidemiological transition, increased longevity and increased exposure to modifiable behavioural risk factors such as unhealthy diet (ie, high in salt, fat and free sugars, and low in fruit and vegetables), physical inactivity, harmful alcohol use and tobacco use.^2^ Although these conditions have been previously observed predominantly among the elderly and non-lean individuals, CVDs are increasingly occurring at younger ages and at lower levels of adiposity in SSA.^3^ This suggests that pathways to CVD risk in SSA may differ from those described in high-income countries, in which these conditions generally manifest later in life and are closely linked to adult lifestyle factors.

The causes of these observed differences remain unknown, but a role for genetics, and for early-life infectious exposures, and undernutrition, which are common in many African countries and often distinct from high-income country populations, has been proposed.^4^ These distinct early exposures may drive different physiological pathways to CVD risk.^5^ Previous studies have demonstrated that important determinants of CVDs begin early in life, with cardiovascular and metabolic changes seen in childhood and adolescence, long before clinical manifestation of CVD in adulthood.^6^ Progress in understanding these pathways in SSA has been constrained by the limited availability of longitudinal studies with detailed life-course data on nutrition, growth, infectious and socio-demographic exposures, and long-term follow-up into adolescence and early adulthood. Although several African birth cohorts have been established, to our knowledge, only one cohort in urban South Africa has investigated associations between early-life and life-course exposures (focusing on sociodemographics and growth) and CVD-related outcomes in late adolescence.^7^

The Entebbe Mother and Baby Study (EMaBS) is a population-based Ugandan birth cohort with extensive socio-demographic, genetic, anthropometric, infection, immunisation, nutrition and immune response data from the prenatal period through to adolescence, together with stored samples from multiple time points across the life course.^8 9^ Data are also available on physiological determinants of CVDs measured at the start of adolescence at 10–11 years.^10^

Between 2024 and 2027, EMaBS participants will reach 21 years of age. This is approaching the end of adolescence, a time of rapid growth and physiological change/turbulence triggered by pubertal hormonal changes, and a time during which behaviours emerge that will determine health in later adulthood; approximately 70% of premature deaths during adulthood are estimated to be the result of health-related behaviours initiated by the end of adolescence.^11^ Assessment at this age, therefore, allows evaluation of key behavioural risk factors initiated during adolescence, including knowledge and understanding of these risk factors, and measurement of physiological determinants of CVDs, which will track into later adulthood.^6^ The EMaBS cohort thus offers a unique opportunity to explore the hypotheses regarding the impact of early-life infectious, nutritional and socio-demographic exposures characteristic of SSA on adult CVD susceptibility.

### Study hypothesis and objectives

The primary hypothesis is that early-life infectious exposures and undernutrition, common in many African settings, influence physiological determinants of CVD measured in early adulthood. Secondary hypotheses are that early-life socio-demographic factors influence knowledge and awareness of CVDs and initiation of risk behaviours for CVDs during adolescence, and that these are associated with physiological determinants of CVDs in this setting.

The study objectives are to: (1) determine the effect of early-life exposures on physiological determinants of CVD in young Ugandan adults; (2) (a) identify determinants of behavioural CVD risk factors and (b) examine their associations with physiological CVD determinants in this population; (3) investigate nutritional and metabolic pathways linking early-life exposures to adult physiological CVD risk; and (4) explore the understanding of CVD risk among participants, including awareness of behavioural risk factors and sources of information on NCDs. In this study, physiological determinants of CVD are defined as blood pressure, blood glucose, insulin, blood lipid levels, body mass index (BMI), and body composition. Behavioural risk factors for CVD include unhealthy diet, physical inactivity, harmful alcohol use and tobacco use (figure 1).

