### Outcomes and exposures

The primary outcomes are physiological determinants of CVD measured in early adulthood, including systolic and diastolic blood pressure, blood lipid concentrations (total cholesterol, high-density lipoprotein cholesterol, low-density lipoprotein cholesterol and triglycerides), BMI, body composition measures (including fat mass and fat-free mass) and markers of glucose metabolism (fasting blood glucose, glycated haemoglobin (HbA1c) and insulin levels). Secondary outcomes include behavioural CVD risk factors, including unhealthy diet, physical inactivity, harmful alcohol use, current tobacco use and poor sleep, assessed using structured questionnaires. Qualitative outcomes include the understanding of CVDs, awareness of behavioural risk factors, perceived personal risk and sources of information on NCDs among participants.

The primary exposures of interest differ by objectives, as shown below.

For objectives 1 and 2a, exposures include early-life infectious exposures (malaria and helminth infections, including *Schistosoma mansoni* and soil-transmitted helminths, measured repeatedly from in utero through childhood), markers of early-life growth and undernutrition (birth weight and growth trajectories), micronutrient status in early childhood (iron indices, vitamin D, vitamin A, vitamin E, zinc, vitamin B12 and folate), inflammatory markers (C-reactive protein) and early-life socio-demographic characteristics (parental education, household socio-economic status and home environment indicators). Selected genetic variants derived from whole-genome data generated from samples collected in early childhood will be considered as secondary exposures.For objective 2b, behavioural risk factors assessed in adolescence and early adulthood (diet, physical activity, alcohol use, tobacco use and sleep quality) will be treated as exposures in analyses examining associations with physiological CVD determinants.For objective 3, analyses will focus on nutritional, infectious, metabolomic and socio-demographic pathways linking early-life exposures to physiological CVD risk in early adulthood. Findings from objective 1 will inform candidate pathways that will include longitudinal infection data, early-life micronutrient and inflammatory markers, metabolomic profiles derived from archived and newly collected samples, and early-life socio-economic conditions.

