We will collect data through questionnaires and physical examination. Questionnaires will be used to update existing socio-demographic information for each participant, collect information on current living conditions, family composition, level of education attained and occupation, and collect information on behavioural risk factors for NCDs, including physical activity, diet, alcohol use, tobacco use, mental health, sleep quality and well-being. Tobacco use will be assessed through self-report, including current and previous smoking status, and number of pack-years. Alcohol use will be assessed through the 30-day Alcohol Use Disorders Identification Test (AUDIT-40), which has been validated against the Timeline Follow Back method, and against phosphatidylethanol in blood for detecting harmful alcohol use in Ugandan youth.^12^ Physical activity will be assessed using the WHO Global Physical Activity Questionnaire, which has been shown to have moderate to high validity and reliability across 12 countries worldwide and was previously used in a Ugandan countrywide survey.^13^ Diet and nutrition will be assessed through food frequency questionnaires, which will include commonly consumed food items from the Uganda regional food surveys; energy and nutrient content will be calculated from available food composition tables; we will focus on high intake of sugar, salt and fat, low intake of fruits and vegetables, and high intake of processed foods. Common mental health disorders will be assessed using the Patient Health Questionnaire−9^14^ and the generalised anxiety disorder−2.^15^ Sleep quality will be assessed using the insomnia severity index.^16^

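### The secondary hypothesis is about starting risk behaviours in adolescence, but the stated tobacco and alcohol outcomes measure current tobacco use and 30-day harmful drinking at about age 21

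*Protocol article*

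**What the plan says.** Under Study hypothesis and objectives, a secondary hypothesis is that early-life socio-demographic factors influence "initiation of risk behaviours for CVDs during adolescence". The Introduction gives a matching reason for the visit at 21: it "allows evaluation of key behavioural risk factors initiated during adolescence".

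Outcomes and exposures lists the behavioural secondary outcomes as "unhealthy diet, physical inactivity, harmful alcohol use, current tobacco use and poor sleep, assessed using structured questionnaires".

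Data collection describes one round of measurement at or near 21 years. For tobacco: "Tobacco use will be assessed through self-report, including current and previous smoking status, and number of pack-years". For alcohol: "Alcohol use will be assessed through the 30-day Alcohol Use Disorders Identification Test".

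The Statistical analysis text for Objective 2a fits logistic regressions to tobacco and to harmful alcohol use. It does not say whether the tobacco variable is current or ever use. For Objective 2b, Outcomes and exposures describes the exposures as "behavioural risk factors assessed in adolescence and early adulthood".

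**The concern.** The hypothesis names an event, starting a behaviour during adolescence. The outcomes name a state, having the behaviour at about 21. No stated outcome is initiation, ever use or age at start.

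The probability of being a current user is the probability of having started multiplied by the probability of having continued. A regression on current use therefore estimates the combined effect of an exposure on both steps. If socio-demographic factors also affect stopping, an association with current use cannot be read as an association with starting. Even if they do not, starters who stopped are lost as events, and precision falls. The concern is confined to a secondary hypothesis and does not touch the primary outcomes.

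**Working it through.** **Hypothesis against outcome**

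| Behaviour | Hypothesis | Stated outcome | Data described | Can starting be recovered? |
|---|---|---|---|---|
| Tobacco | Initiated in adolescence | Current use | Current and previous smoking, pack-years | Yes, as ever smoked; age at start is not named |
| Alcohol | Initiated in adolescence | Harmful use | 30-day instrument | Not from this instrument, if harmful use ended before the window |

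**Illustration of size**

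The plan has no figure of its own to reproduce: Table 1 covers blood pressure and lipids only. From Sample size determination I take N = 900, a two-sided 5% level and 30% exposure prevalence, which is one row of Table 1. This gives 270 exposed and 630 unexposed. All starting and persistence rates below are assumptions.

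Let p1 and p2 be the proportions of exposed and unexposed who ever started, and r1 and r2 the proportions of starters still using at 21. Then:

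- Current use = p1 × r1 in the exposed and p2 × r2 in the unexposed.
- OR = [a/(1 − a)] / [b/(1 − b)] for proportions a and b.
- Power = Φ[(|a − b| − 1.96 × SE0) / SE1], where SE0 uses the pooled proportion and SE1 the separate proportions.

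Ever use, 0.24 v 0.15: OR = (0.24/0.76)/(0.15/0.85) = 1.79. SE0 = 0.02776 and SE1 = 0.02963. Power = Φ[(0.09 − 1.96 × 0.02776)/0.02963] = Φ(1.20) = 0.885. Expected events = 270 × 0.24 + 630 × 0.15 = 159.

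*Equal persistence in both groups*

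| Persistence | Current use, exposed v unexposed | OR | Power |
|---|---|---|---|
| 100% (ever use) | 0.240 v 0.150 | 1.79 | 0.89 |
| 75% | 0.180 v 0.1125 | 1.73 | 0.76 |
| 50% | 0.120 v 0.075 | 1.68 | 0.58 |
| 33% | 0.079 v 0.0495 | 1.65 | 0.42 |

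The risk ratio stays at 0.24/0.15 = 1.60 throughout. The small drift in the OR is only the OR approaching the risk ratio as the outcome becomes rarer. The cost is lost events: 159 become about 80 at 50% persistence.

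*Persistence that differs by exposure*

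| Ever started (exposed v unexposed) | Persistence (exposed v unexposed) | Current use | OR for starting | OR for current use |
|---|---|---|---|---|
| 0.24 v 0.15 | 40% v 60% | 0.096 v 0.090 | 1.79 | 1.07 |
| 0.24 v 0.15 | 60% v 40% | 0.144 v 0.060 | 1.79 | 2.64 |
| 0.20 v 0.20 | 40% v 60% | 0.08 v 0.12 | 1.00 | 0.64 |
| 0.20 v 0.20 | 60% v 40% | 0.12 v 0.08 | 1.00 | 1.57 |

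*A second set of assumptions* (450 per group, ever started 0.30 v 0.20) shows the same pattern. The OR for starting is 1.71 with power 0.94. If 40% of starters stop in both groups, the OR is 1.61 with power 0.71. If 40% of exposed and 20% of unexposed starters stop, the OR is 1.15. If those stopping rates are reversed, it is 2.32.

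**The case against.** The best reply is that the word for initiation is loose framing in one sentence. Objective 2a itself speaks of determinants of behavioural risk factors, not of starting them. Diet and physical inactivity have no natural starting event. Current use is a legitimate outcome for later cardiovascular risk. The list of secondary outcomes is not said to be exhaustive, and the Objective 2a analysis text leaves the tobacco variable open, so the full protocol may settle it. All this makes the point a matter of alignment. It does not remove it, because the article states both a hypothesis and an outcome, and they are different quantities.

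Four stronger readings are tempting, and the document does not support them.

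- *Ex-smokers are treated as people who never started.* They are not. Previous smoking and pack-years are recorded, so they can be told apart from never-smokers. They are non-events only under a current-use outcome.
- *People who drink below the harmful level are misclassified.* Study hypothesis and objectives itself names harmful alcohol use as the risk factor, so such drinkers are correctly non-events. What remains is harmful use that began and ended before the 30-day window.
- *The Objective 2b description of behaviours assessed in adolescence is wrong.* Study populations and recruitment reports 976 participants seen at 15–18 years without itemising what was measured. A condensed article's silence does not show that behavioural data are absent.
- *The odds ratio will be badly distorted.* The large distortions above all need persistence to differ by exposure, and the article gives no information on that.

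**Conclusion.** The point holds in limited form. As the article is worded, no stated outcome measures the initiation that the secondary hypothesis is about, although the tobacco data needed for a closer measure are already being collected. For alcohol, the named instrument cannot identify harmful use that had ended before its window.

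On assumed rates and equal persistence, the consequence is mainly lost power: 0.89 to 0.58 at 50% persistence, within a range of 0.76 to 0.42 for persistence of 75% to 33%, with the OR between 1.73 and 1.65 instead of 1.79. Bias beyond that small drift arises only if persistence differs by exposure. This is possible for socio-demographic exposures, but its size is unknown. These figures are unadjusted illustrations, not estimates for this cohort. The change is worth making because it is cheap and clarifies what Objective 2a can claim.

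**What to change.** **Tobacco.** In Outcomes and exposures, and in the Objective 2a analysis text, define ever tobacco use (current or previous, from the smoking-status items) as the outcome that tests the initiation hypothesis. Keep current use as a second outcome. The cost is wording and one recode, with no new data. The downsides are reliance on recall and the inclusion of brief experimentation. Ever use also does not date the start, so it includes anyone who began shortly before the visit.

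**Alcohol.** Either restate the hypothesis as harmful alcohol use at about 21 years, which is wording only, or, if the adolescent visits recorded alcohol use, define an outcome from those data and say so.

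**Timing.** Name the visits at which the Objective 2b behaviours were assessed. If adolescent behavioural data exist, they bear directly on the initiation hypothesis too.

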**Figure 1 F1:**
[figure not shown]
Conceptual framework for the Entebbe Mother and Baby Study at 21 year. BMI, body mass index; CVD, cardiovascular disease.

## Methods and analysis

### Planned start and end dates for the study

The planned start date for this study is 22 October 2024, and the planned end date is 31 March 2027.

### Study design

This is a new round of data collection in a longitudinal study. It will leverage and extend the existing EMaBS birth cohort. The participant data collected in this new round will be linked to earlier individual data collected from pregnancy through childhood to date. The new round of data collection began on 22 October 2024, and is currently ongoing.

### Patient and public involvement statement

Involvement of the participants and the broader community has been fundamental to study preparation, enrolment and ongoing follow-up. During the planning stages of the study, meetings were held with community leaders to explain the planned research questions and obtain input into the conduct of the study. Each village in the study area has an elected committee, and at the start of EMaBS, each of these committees appointed volunteer assistants (‘community field workers’), members of the public who have played a key role in the study. They continue to provide valuable support to EMaBS through follow-up and engagement activities. More recently, the Medical Research Council/Uganda Virus Research Institute and London School of Hygiene & Tropical Medicine (MRC/UVRI and LSHTM) Uganda Research Unit has established a community advisory board, which has also been engaged in meetings to discuss this work in the cohort. This has been complemented by meetings with participants and their parents and caregivers to obtain their input into the project plans.

### Study populations and recruitment

The study will be conducted among EMaBS participants, who will be contacted and invited to participate in Entebbe Mother and Baby Study at 21 years (EMaBS@21). The EMaBS birth cohort began life as a randomised controlled trial aimed at investigating the impact of anthelmintic treatment during pregnancy and early childhood on responses to immunisations, incidence of infectious and allergy-related diseases, and growth and nutrition (ISRCTN32849447).^9^ A total of 2345 documented live-born children were recorded in the cohort between 2003 and 2006. EMaBS cohort attrition due to mortality or loss to follow-up was highest during the first 5 years of life (27% in infancy, 45% from birth to 5 years) and has stabilised at an average of ~2% per year since then. For example, 1270 participants were seen at age 5 years, 1119 at age 10–11 years and 976 were seen at the EMaBS clinic when aged 15–18 years. In April 2023, we undertook a cohort census in concert with a dissemination open day. A total of about 1500 cohort participants, over half of whom attended the open day, have provided comprehensive location and contact details and expressed willingness to be contacted to take part in future waves of data collection. We will use a census-based sampling approach for this study, that is, we plan to sample as many EMaBS participants as are available and meet the eligibility criteria within the recruitment time frame.

